### Intervention and control

In the control group, the ACN will carry out usual care, which involves a clinical inspection, measurements of vital signs (respiratory rate(breaths/min), saturation (%), blood pressure (mmHg), heart rate (beats/min), body temperature (C^0^), and Glasgow Coma Scale [36]), and POCT for CRP and haemoglobin.

The intervention group will receive extended POCT in addition to usual care. Extended POCT includes a FLUS and biochemical blood analyses. Biochemical blood analyses include sodium, potassium, creatinine, urea, and leucocytes with differential count.

In both control and intervention groups, the ACN communicates the examination results to the participants’ PCP through telephone communication and electronic message (EdiFact) for written documentation. The communication to the PCP is part of usual care and is carried out in both groups.

Preceding to commencement of the study, all ACNs undergo comprehensive training in FLUS, technical procedure of POCT biochemical blood-analysis, as well as training in research methods with a specific emphasis on study procedures. This training is designed to enhance their adherence to and compliance with the randomization procedure and protocol.

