***Secondary outcomes***		
Outcome 2	Hospital admissions at Day 0^a^	Proportion of hospital admission at Day 0^a^
Outcome 3	Readmission ≤ 30 days	Proportion of readmissions within 30 days follow-up (Day 1 to Day 30)
Outcome 4	Mortality ≤ 30 days	Number of deaths within 30 days follow-up (Day 0^a^ to Day 30)
Outcome 5	Length of hospital admission	Number of days admitted
Outcome 6	Hospital-free days ≤ 30 days	Number of days alive that is spend outside of an acute-care hospital, long-term acute-care hospital or in an emergency department. Days spent wholly or in part under “observation” status counts as hospital days [44]
Outcome 7	Complications during hospital admission	Number of complications during admission, registered in the electronic patient journal
Outcome 8	Treatment initiations or changes at Day 0^a^	Number of treatment initiations or changes at Day 0^a^
Outcome 9	Treatment initiation or changes ≤ 30 day	Number of treatment initiations or changes within 30 days follow-up (Day 1 to Day 30)
Outcome 10	Functional level	Proxy assessment of functional level: - Change in amount of home care within 30 days follow-up - Number of changes of dwelling
Outcome 11	Re-referrals to the ACHCS	Number of re-referrals to the ACHCS
Outcome 12	Contact to the PCP ≤ 30 days	Number of contacts to the PCP within 30 days follow-up (Day 0^a^ to Day 30)

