### Statistical analyses

Statistical analysis will be carried out using STATA® (StataCorp LLC, Texas, USA).

Data analysis will be conducted according to intention to-treat principles and include all eligible participants with available outcome data. Missing data will be reported for each variables, including reasons. Imputation and sensitivity analysis will be used to assess the potential biases caused by missing outcome data.

Descriptive statistics for both groups will be summarised including demographic and baseline characteristics: patient symptoms, referring health professional, Clinical Frailty Scale (CFS) [45, 48], co-morbidities, daily medication, amount of home care, alcohol consumption, smoking, BMI, vital signs (blood pressure, pulse, oxygen saturation, respiratory frequency, and ear temperature), treatment initiations or changes, admissions, re-referrals to the ACNs, contacts to the PCPs, and mortality.

In the intervention group, descriptive statistics will also include POCT measurements and FLUS findings.

Categorical data will be reported as numbers and percentages. Continuous data will be presented as means (SD) on normally distributed data and medians [IQR] with range on non-normally distributed data. Differences in baseline characteristics between the intervention group and control group will be calculated using Chi-squared test, Fischer’s exact test, and Wilcoxon-Mann–Whitney test as appropriate. The statistical significance threshold for all tests is *p* < 0.05.

For the primary outcome univariate and multivariate logistics regression models will be used to investigate risk of admission between groups.

Univariate and multivariate logistic regression models will be used to compare secondary outcomes between the two groups.

Both regression models will be adjusted for possible confounders (gender, age, civil status, co-morbidity, alcohol consumption, smoking, living alone, and BMI).

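### Logistic regression is the only between-group model named for the secondary outcomes, yet 8 of the 11 are defined as days, event counts or change in home care

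*Protocol article*

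**What the plan says.** The Statistical analyses section of the protocol article gives one rule for the secondary outcomes: "Univariate and multivariate logistic regression models will be used to compare secondary outcomes between the two groups". No outcome is exempted, and no linear, count, ordinal or rank-based model is named for any of them. The same section names chi-squared, Fisher and Wilcoxon-Mann-Whitney tests, but for differences in baseline characteristics. Means and medians appear there as ways of presenting continuous data, not as comparisons.

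Table 1 (Outcomes section) defines the secondary outcomes. Length of hospital admission is "Number of days admitted". Hospital-free days begin with "Number of days alive that is spend outside of an acute-care hospital". Contact to the PCP is "Number of contacts to the PCP within 30 days follow-up". Complications, treatment initiations or changes (two windows), re-referrals and changes of dwelling are also numbers, and home care is a change in amount. The table gives no threshold for any of these.

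**The concern.** A binary logistic model estimates an odds ratio for a yes/no event. It does not estimate a difference in days, a ratio of event rates or a change in hours of care. To use it on outcomes 5 to 12, someone must first turn each into yes/no, and the article does not say how.

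These outcomes carry part of the trial's argument. The Background predicts effects on length of stay, amount of home care and functional status. The Discussion (Over-diagnosing and over-treatment) accepts that admissions could rise and says that benefit might still show in those same measures. If the primary result is null or adverse, interpretation will lean on outcomes for which the article names no fitting model. Participants, nurses and PCPs all know the allocation, so it helps if the form of each analysis is beyond dispute beforehand.

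**Working it through.** **Classifying the outcomes.** Inputs are the outcome measures in Table 1, outcomes 2 to 12.

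| Outcome | Measure | Type per participant | Cut-point stated |
|---|---|---|---|
| 2 | "Proportion of hospital admission at Day 0" | binary | not needed |
| 3 | "Proportion of readmissions within 30 days follow-up" | binary | not needed |
| 4 | "Number of deaths within 30 days follow-up" | binary (worded as a number, but 0 or 1 for each person) | not needed |
| 5 | length of stay | days | none |
| 6 | hospital-free days | days | none |
| 7 | complications | count | none |
| 8, 9 | treatment initiations or changes, two windows | count | none |
| 10 | home care; dwelling | change in amount; count | none |
| 11 | re-referrals | count | none |
| 12 | PCP contacts | count | none |

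Binary: 3. Not binary: 11 − 3 = 8.

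Within the eight, complications, treatment changes, re-referrals and the dwelling part of outcome 10 have a natural any/none split, although the table defines them as numbers. Length of stay, hospital-free days, change in home care and PCP contacts do not.

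**The plan's own figure.** The only computed figure is the sample size for the primary outcome. With 31% against 21%, two-sided alpha 0.05 (the article does not state sidedness), power 0.80 and pooled variance:

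n = [1.960·√(2·0.26·0.74) + 0.842·√(0.31·0.69 + 0.21·0.79)]² / 0.10² = 301 per arm, 602 in total, as stated.

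The point does not depend on it; 301 serves only as the arm size below.

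**What dichotomising might cost.** The article gives no means or distributions, so this is an illustration under my assumptions: Poisson counts, rate ratio 0.8, 301 per arm, two-sided 0.05.

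- Count model: power = Φ(|ln 0.8|/SE − 1.96), with SE = √(1/(301·m) + 1/(301·0.8m)). For control mean m = 2, SE = √(1/602 + 1/481.6) = 0.0611, so power = Φ(0.223/0.0611 − 1.96) = 0.95.
- Dichotomised: power for comparing P(Y ≥ k) between arms with the pooled two-proportion test, which stands in for an unadjusted logistic model.

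| Control mean | Count model | ≥1 | ≥2 | ≥3 | ≥4 | ≥5 |
|---|---|---|---|---|---|---|
| 0.5 | 0.45 | 0.37 | 0.26 | 0.11 | 0.05 | 0.03 |
| 1 | 0.73 | 0.53 | 0.57 | 0.38 | 0.18 | 0.08 |
| 2 | 0.95 | 0.59 | 0.83 | 0.84 | 0.71 | 0.46 |
| 4 | >0.99 | 0.37 | 0.83 | 0.97 | 0.99 | 0.98 |

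For an any/none split of a Poisson count with mean μ, the share of information kept is μ/(e^μ − 1): about 95% at 0.1, 90% at 0.2, 58% at 1 and 31% at 2. The loss is therefore small for rare events and large for frequent ones. Real counts are likely to be overdispersed, which would lower the count-model figures.

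**The case against.** Four objections deserve an answer.

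*The sentence says logistic, not binary logistic.* A proportional-odds model is a form of logistic regression and would suit days. That is true, but ordinal regression is not named, and the same phrase is used for the primary outcome, which is binary. If an ordinal model is meant, saying so removes much of the problem for days and home care.

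*Rank tests may be available.* The descriptive list in Statistical analyses mixes baseline variables with follow-up variables such as treatment changes, re-referrals and PCP contacts, and the Wilcoxon test follows soon after. On a loose reading it could reach some counts. The test sentence is nevertheless confined to baseline differences. Length of stay, hospital-free days, complications and dwelling changes are not in that list, and a rank test alone gives no adjusted effect estimate.

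*Models and cut-points belong in an analysis plan that is not shown.* A condensed article may leave them out. This one does not: it states a model, and that model does not fit most of its own table. One cannot conclude, though, that cut-points will be chosen after the data are seen, because a plan may already define them.

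*Any/none is natural for some of these outcomes.* It is, for roughly half of the eight. Table 1 still defines those as numbers.

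Three stronger readings are tempting and not supported:

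- A reader might infer that the trial cannot report its numbers at all. The descriptive statistics by arm expressly include treatment changes, re-referrals and PCP contacts. What is missing is a model-based effect on the stated scale.
- A reader might apply the textbook loss from a median split of a normal variable (2/π, about 0.64 of the information kept). That presumes normal data, and most of these outcomes are counts or days that may include many zeros.
- A reader might infer from "The communication to the PCP is part of usual care and is carried out in both groups" that nearly every participant has at least one PCP contact on Day 0, so that a model for outcome 12 would break down. Table 2 takes that outcome from the Danish health registries, which Data sources describes in terms of consultations. Nothing shows that the nurse's call or message is counted there, and the article proposes no any/none split. The documents give no reason to change its window.

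**Conclusion.** The concern holds: a stated rule does not match the stated measures. The article prescribes logistic regression for the secondary outcomes and names no alternative, while 8 of the 11 are days, counts or changes without a cut-point. The count of eight rests only on Table 1, reading mortality as 0/1 per participant. Four outcomes lack any natural split: length of stay, hospital-free days, change in home care and PCP contacts.

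The statistical cost cannot be fixed from the documents. Under the Poisson illustration it runs from slight to severe, and with a control mean of 2 the choice of cut-point alone moves power between 0.46 and 0.84. The primary outcome, its model and the sample size are untouched. This should be fixed, but it does not threaten the main result.

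**What to change.** Replace the blanket sentence with a model for each outcome:

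- Outcomes 2, 3 and 4: keep logistic regression.
- Outcomes 7, 8, 9, 11, 12 and changes of dwelling: negative binomial regression, or Poisson with robust standard errors, reporting rate ratios.
- Outcomes 5 and 6: a proportional-odds model, or a mean difference with a bootstrap or robust confidence interval.
- Home care in outcome 10: a linear or ordinal model adjusted for the baseline amount.

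If a yes/no version of any outcome is wanted, state its cut-point and reason in advance and present it beside the analysis on the defined scale. If an analysis plan already names such models, bring the article's sentence into line with it. The cost is a short paragraph and a few lines of Stata code, with no new data and no change in sample size.

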***Primary outcome***		
Outcome 1	Hospital admissions ≤ 30 days	Proportion of hospital admissions within 30 days follow-up (Day 0^a^ to Day 30)

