### Data collection

During the in-home assessment participants will undergo a systematic screening and examination program, which include registration of age, gender, alcohol consumption, smoking, BMI, nationality, comorbidity, polypharmacy, place of assessment, symptoms of infection, days with symptoms, Clinical Frailty Scale [45], vital signs (blood pressure, pulse, oxygen saturation, respiratory frequency, and ear temperature), and POCT for analyses of CRP and haemoglobin.

In addition, the intervention group will undergo the extended POCT examinations (FLUS and biochemistry on blood analysis).

Outcomes for the 30 days-follow up period are collected from electronic databases. Table 2 provides an overview of the data-sources and corresponding time-points for each outcome.

**Table 2 Tab2:** Time point and data-sources for primary and secondary outcomes

	**Day 0**^**a**^			**Follow up: 30 days**			
	**During in-home assessment**	**ESCR**	**Danish health registries**	**ESCR**	**EPJ**	**FMK**	**Danish health registries**

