### Data analyses

#### Sample size and statistical power

A parallel group design with a 1:1 allocation ratio and a superiority design was chosen for this trial. To our knowledge, the number of patients acutely admitted after a visit from ACNs are unknown. Preliminary results from a pilot-study of the intervention (not yet published) showed that 21% of included participants were acutely admitted after a visit from ACNs. We aimed to detect a clinically significant absolute reduction in acute hospital admission of 10%. Therefore, based on data from the unpublished pilot-study, we aimed in detecting a reduction from 31 to 21% at a significance level 0.05 with a power of 0.80, requiring a total of 602 participants (301 in each arm). Allowing for a 5% dropout after randomisation, 316 in each arm are required (a total of 632 participants).

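### Adjustment covariates are chosen as confounders and leave out likely prognostic baseline data already recorded, so the adjusted analysis forgoes a modest gain in power

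*Protocol article*

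**What the plan says.** The primary outcome is binary: "Proportion of hospital admissions within 30 days follow-up", counted from the day of inclusion (Table 1). The Statistical analyses section plans univariate and multivariate logistic regression for it and for the secondary outcomes, then fixes the covariates: "Both regression models will be adjusted for possible confounders (gender, age, civil status, co-morbidity, alcohol consumption, smoking, living alone, and BMI". Neither model is named as primary.

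The Data collection section lists what is registered for every participant at the home visit. This includes "symptoms of infection, days with symptoms, Clinical Frailty Scale", vital signs, place of assessment, and "POCT for analyses of CRP and haemoglobin". The Statistical analyses section uses symptoms, frailty and vital signs only to describe the groups. It gives no reason for keeping them out of the models.

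The same section bases the analysis on everyone eligible who has outcome data, and mentions imputation for missing outcomes. It does not say what happens when a covariate is missing.

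**The concern.** Randomisation removes systematic confounding, so the word gives the wrong selection rule. Baseline covariates are useful here to the extent that they predict admission. In a logistic model, prognostic covariates raise the power of the treatment test.

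The article's own reasoning points to variables that are not on the list. Study setting says the assessment results, vital signs and CRP among them, go to the physician and inform the decision. Eligibility mixes cough, dyspnoea and fever with falls and functional decline, so presenting symptom separates quite different patients. Civil status and living alone, by contrast, carry much of the same information, and living alone is hard to define for the care-home and rehabilitation-centre residents who may be enrolled.

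At stake is power that data already in hand could supply to the adjusted analysis of the primary outcome.

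**Working it through.** **1. The plan's own figure.** Inputs from Sample size and statistical power: "we aimed in detecting a reduction from 31 to 21" per cent, "at a significance level 0.05 with a power of 0.80", allocation 1:1. Sidedness is not stated; two-sided is assumed.

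n per arm = [1.960 × √(2p̄(1−p̄)) + 0.842 × √(p₁(1−p₁) + p₂(1−p₂))]² / (p₁−p₂)², with p̄ = 0.26.

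- First term: 1.960 × √0.3848 = 1.216
- Second term: 0.842 × √(0.2139 + 0.1659) = 0.842 × √0.3798 = 0.519
- n = (1.216 + 0.519)² / 0.01 ≈ 301

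This matches the article: "requiring a total of 602 participants (301 in each arm". Power at 301 per arm is 80.0%; at 316 per arm it is 81.9%. A one-sided test would need only 237, so the stated number is two-sided. No covariate enters the calculation, so the planned 80% does not depend on adjustment.

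**2. What the covariate choice changes.** The article reports no prognostic strength, so it has to be assumed. Simulation: 301 per arm, marginal admission rates held at 31% and 21%, 4,000 trials per scenario, two-sided Wald test of treatment at 0.05. The listed set is one normal score with log-odds SD 0.3 or 0.5. The omitted set is a second, independent score with SD 0 to 1.4. The Monte Carlo standard error of each power is √(0.8 × 0.2 / 4000) = 0.6 points. Gain is the last power column minus the one before it.

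| SD listed | SD omitted | AUC, both sets | Unadjusted | Listed set | Listed + omitted | Gain (points) |
|---|---|---|---|---|---|---|
| 0.3 | 0 | 0.582 | 80.6% | 81.1% | 81.0% | −0.1 |
| 0.3 | 0.4 | 0.636 | 80.7% | 81.4% | 82.7% | 1.3 |
| 0.3 | 0.7 | 0.695 | 79.3% | 79.8% | 83.6% | 3.8 |
| 0.3 | 1.0 | 0.750 | 80.3% | 80.3% | 85.5% | 5.2 |
| 0.3 | 1.4 | 0.805 | 80.4% | 80.7% | 90.2% | 9.5 |
| 0.5 | 0.5 | 0.683 | 81.0% | 82.6% | 83.6% | 1.0 |
| 0.5 | 0.7 | 0.716 | 81.2% | 82.1% | 85.0% | 2.9 |
| 0.5 | 1.0 | 0.761 | 81.5% | 82.6% | 87.6% | 5.0 |
| 0.5 | 1.4 | 0.814 | 80.3% | 81.8% | 90.3% | 8.5 |

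The listed set gives about 80 to 83%, so it does not take power below plan. Adding the omitted variables gains about 1 to 5 points for a combined AUC of roughly 0.64 to 0.76, and 8.5 to 9.5 points at about 0.81. If they carry no information (first row), power is essentially unchanged.

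**3. Which variables are fixed before allocation.** The nurse checks the inclusion criteria and obtains consent (Recruitment and enrolment), then registers the participant and the database allocates (Randomization, allocation, and implementation). Presenting symptom is an eligibility criterion, so it is known by then. Place of assessment is where the nurse already is. For frailty, vital signs and CRP the order is not stated: Data collection places them during the visit, and Intervention and control describes vital signs and CRP as part of the care given in each arm.

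**The case against.** The best defence is that the list is pre-specified and that adjusting for it is valid in a randomised trial. It contains age and co-morbidity, which any replacement would keep. A demographic and co-morbidity set is also a cautious choice in an open-label trial, because a nurse who knows the arm could rate frailty differently. Adjusting for a value recorded after allocation could introduce bias. This stands, and it limits the fix to values fixed before allocation. It does not explain the omission of presenting symptom.

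It is also fair that, if the univariate model turns out to be primary, the covariates do not touch the primary test. The adjusted model is nevertheless a planned analysis of the primary outcome.

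Four stronger readings are tempting, and the article does not support them:

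- **That the plan gives away power.** The 80% is unadjusted and is kept; only an additional gain is forgone.
- **That the omitted variables are the strongest predictors and the listed ones weak.** The first is clinically plausible, but nothing in the article quantifies either.
- **That missing BMI, alcohol or smoking data would cut power to about 76%.** This needs an assumed 10% missing (about 60 of 602, leaving about 271 per arm) and a complete-case rule that the article never states. Handling of missing covariates may sit in an analysis plan that is not shown.
- **That civil status and living alone are not collected.** They are absent from the Data collection list, but that list is not worded as exhaustive and the article condenses a fuller protocol.

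**Conclusion.** The point holds as a moderate matter of efficiency. The stated basis for choosing covariates is wrong for a randomised trial, likely prognostic variables already recorded in both arms are left out, and two listed covariates overlap. The sample size stands.

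The forgone gain is about 1 to 5 percentage points of power at moderate prognostic strength and up to about 10 if it is very strong. It applies only to the adjusted model and rests on assumed prognostic strength. It would shrink if frailty, vital signs and CRP prove to have been recorded after allocation and cannot be used. Converting the gain into a large sample-size equivalent would lean on the most favourable of these assumptions and is not warranted.

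**What to change.** Before any analysis by arm:

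- Replace the list with a short set described as prognostic: age, sex, co-morbidity, presenting symptom (respiratory or fever versus fall or functional decline) and place of assessment.
- Add Clinical Frailty Scale, oxygen saturation, respiratory rate and CRP only where they were recorded before allocation.
- Keep at most one of civil status and living alone.
- State that a missing baseline covariate is handled by simple imputation or a missing category, so that the adjusted model includes everyone with outcome data, as the section promises.

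The variables are already collected, so the cost is revised wording and a little more analysis work. The order of recording relative to allocation has to be established, and frailty ratings or measurements made after allocation must be left out, with the corresponding loss of gain.

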### Dissemination

The trial outcomes will be disseminated through publications in peer-reviewed journals and presentations at both national and international conferences. Layman-friendly project reports will be distributed to all participants, and comprehensive reports will be forwarded to Kolding Municipality. Social media platforms will be strategically employed to communicate results to a broader audience, encompassing both national and international perspectives.

